### Participation and retention

We will collect data on participant and provider participation and retention. Participant participation is defined as the number of eligible participants (i.e., met inclusion criteria for screening one and two) who agreed to participate in the feasibility trial. Participant retention is the number of participants who were randomized to the intervention condition who completed intervention sessions one, two, three, four, and/or five, as well as the number of all participants in the feasibility trial who completed the post-assessment, 1-month follow-up, and 3-month follow-up. Provider participation includes the number of providers who agreed to participate out of the total number who were offered the opportunity to participate. In addition, we will gather data on the number of providers trained to deliver the intervention, and the number who ultimately were rated highly enough on their clinical skills and knowledge of trauma and PTSD to be eligible to be providers during the pre-pilot and pilot. In addition, when participants, caregivers, and staff are offered or trained in the intervention but decline to participate, they will be asked to complete a brief interview assessing reasons for non-participation.

Quantitative data will be entered using REDCap software with smartphones and uploaded to a secure encrypted server. Data will be downloaded to a password protected and encrypted computers at UCLA facilities and Ethiopia field site. All paper data files and audio recorders will be kept securely stored in a locked file cabinet in a locked office at field site. Qualitative data and audio recordings will be uploaded to secure encrypted server and downloaded to a password protected and encrypted computer. Data management reports across the three following domains will be employed: entered, verified, and edited. These reports of data records will be evaluated once a month.

Ongoing supervision will be achieved through weekly phone calls and at least three times per year annual site visits, virtual or neighboring site personnel, to provide training and supervision. Study coordinators will ensure consistency of procedures, problems/challenges, and general training issues. For example, will address issues of data collection, budget, recruitment, data management and analysis, and perform training and ongoing review of the protocol and assessment procedures. Data will be examined weekly and feedback provided to research staff to make any corrections in as close to real time as possible.

### Randomization

Starting with the sixth participant enrolled (the first five participants will be in the pre-pilot), participants will be randomized to receive the intervention or treatment as usual (TAU) which includes medication management and follow-up at the health facilities. There are currently no other psychotherapies available so TAU was chosen as the comparator. The sixth to the 50^th^ participant (45 participants to be randomized to account for potential dropout) will be randomly assigned with a 1:1 allocation using a computer-generated randomization schedule that will be created by the PI. After screening is complete, researchers will run a randomization computer program to identify the assigned treatment arm. Researchers will then record the participant ID number and treatment arm in the study log and will also record the participant’s treatment arm in their medical chart. Researchers will then notify the health provider of the participant’s allocation and the date and time the participant will start the treatment or TAU. Participants, research staff, and psychiatric nurses conducting the pre, post, and follow-up assessment will be masked to the participant’s condition.

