#### Clinical diagnosis and characteristics

Health providers will be asked to complete a short form about participant diagnosis, medication name, dose, and frequency as well as whether the participant has been adherent to medication during the last 3 months. Participant psychiatric diagnoses, medication, dates of attended mental health visits during the year prior to the baseline assessment and up through the 3-month follow-up, and length of psychiatric illness will be extracted from medical records at the health center.

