#### Intervention satisfaction

Participants and caregivers will complete satisfaction ratings that have been developed and validated in Ethiopia [47] during their post-assessment and providers will complete ratings of their perception of participant satisfaction, after the participant’s last treatment session.

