**Assessments**								
*Sociodemographics questionnaire*	X				X	X	X	
*Life Events Checklist for DSM-5*	X				X	X	X	
*adapted PTSD Checklist for DSM-5* (PCL-5)	X				X	X	X	
*WHO Disability Assessment Schedule II WHODAS-2 (12-item)*	X				X	X	X	
*Clinician Administered PTSD Scale for DSM-5 (CAPS-5)*		X			X	X	X	
*Brief Psychiatric Rating Scale Expanded Version 4.0 (BPRS-4.0)*		X			X	X	X	
*Suicidal Ideation module of the CIDI*		X			X	X	X	
*adapted PTSD Knowledge Test*		X			X	X	X	
*Internalized Stigma of Mental Illness Scale (ISMI-10)*		X			X	X	X	
*Post-Traumatic Cognitions Inventory*		X			X	X	X	
*The Self-Assessment Manikin (SAM)*		X			X	X	X	
*PhenX Toolkit’s trauma challenge assessment*		X			X	X	X	
*Use of Stress Management Strategies*		X		X	X	X	X	
*Fast Alcohol Screening Test (FAST)*		X			X	X	X	
*Patient Health Questionnaire (PHQ-9)*		X			X	X	X	
*Intervention and healthcare satisfaction ratings*					X			
*Qualitative interview*					X	X		

The time from initial contact to each assessment and each treatment session will be tracked. To allow for scheduling flexibility, participants will be able to complete each assessment up to 1 week before or after the target assessment date, for a total of a 2-week assessment window for the 1-month and 3-month follow-ups, and a 1-week assessment window for the post-assessment.

Since intervention participants may take between 5 weeks to 5 months to complete the intervention, participants in the TAU condition will be matched by study enrollment date and health center location to a participant in the intervention condition, and will complete follow-up dates on the same schedule. Since interview times may differ by participant, participants will be told they will complete five sessions and four interviews during the study, but will not be told the assessment schedule in advance.

Assessments will take place at the primary care center or hospital, unless this is not feasible for participants. If participants cannot come to the primary care center for assessments, then the assessments will be completed in participant’s homes or another location of their choice. All intervention and TAU sessions will take place in the health care center, and all participants will continue concomitant medication management and follow-up care.

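### Participants are declared masked in a psychotherapy-versus-usual-care trial, which is not credible, and the planned masking of assessors is weakly protected

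*Protocol article*

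**What the plan says.** The Randomization section states: "Participants, research staff, and psychiatric nurses conducting the pre, post, and follow-up assessment will be masked" to allocation. The same section describes participants as "randomized to receive the intervention or treatment as usual (TAU) which includes medication management and follow-up at the health facilities", and explains the choice of control: "There are currently no other psychotherapies available so TAU was chosen as the comparator".

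On who handles allocation, it has researchers run the randomization program after screening. It continues: "Researchers will then record the participant ID number and treatment arm in the study log and will also record" the arm in the participant's medical chart, after which they notify the provider.

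Four other places bear on masking:

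- **Feasibility trial assessment schedule.** The data collectors and psychiatric nurses who do the quantitative assessments are described as masked. Qualitative interviews go to someone else, expressly to keep the blind.
- **Clinical diagnosis and characteristics.** Diagnoses, medication and "dates of attended mental health visits during the year prior to the baseline assessment and up through the 3-month follow-up" are extracted from the health-centre records.
- **Use of stress management strategies.** This measure is for the intervention arm, is taken by therapists during homework review, and is checked by fidelity raters from recordings. Table 1 nevertheless marks "Use of Stress Management Strategies" at enrolment, post-treatment, 1 month and 3 months as well as during sessions.
- **Intervention satisfaction.** "Participants and caregivers will complete satisfaction ratings that have been developed and validated in Ethiopia" at the post-assessment.

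**The concern.** A masking statement tells the reader which biases can be discounted. If participants are said to be masked, a reader will take the self-reported symptom scores to be protected from expectancy and from reporting that follows knowledge of treatment. If they are not masked, that protection is absent from most of the outcomes.

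A second question is whether the assessors' masking survives the plan's own procedures, because CAPS-5 and BPRS-4.0 depend on it.

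The trial is a feasibility study, but this still matters. The Quantitative data analyses section gives particular attention to change from baseline to post-intervention and to the comparison of intervention with TAU, and uses the results to inform a fully powered trial. Testing trial procedures is itself a stated goal of the design, and masking is one of those procedures.

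**Working it through.** The plan gives no figure to reproduce here. The check sets each group said to be masked against the described procedures, and then counts outcomes by who supplies the score.

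**1. Participants**

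- The Intervention section has breathing retraining taught in session one and revisited in every later session, alongside psychoeducation with handouts and worksheets, and positive coping.
- The comparator is medication management and follow-up. No sham or attention control is described.
- In step two of screening, the nurse assesses capacity to consent to BREATHE by name. Eligibility also requires capacity to consent to randomization. Participants therefore know that a named treatment exists and that they may or may not receive it.
- The only concealment described is that participants are told to expect five sessions and four interviews, without the assessment timetable. That hides the schedule, not the content of the sessions.

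The phrase about conducting assessments cannot qualify the word participants, because participants do not conduct assessments. The statement is wrong for this group.

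**2. Research staff and nurses**

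- The assessment schedule section plans masked assessors, so masking is possible for this group.
- The Randomization section has researchers generate, log and chart the arm. The text under Qualitative interviews says that all interviews and assessments are done by trained researchers. No section says that these are different people.
- The chart that carries the arm is also a source of study data up to the 3-month follow-up. Who extracts the data, and when, is not stated.
- Strategy use is confined to one arm and to therapists in its own section, but Table 1 places it at four time points outside the sessions. The two cannot both be followed as written.

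**3. Count of two-arm outcomes in Table 1**

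Table 1 lists 17 assessment rows. Setting aside sociodemographics, the Life Events Checklist, strategy use, satisfaction and the qualitative interview leaves 17 − 5 = 12.

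| Source of score | Measures | Number |
|---|---|---|
| Participant | PCL-5, WHODAS, PTSD Knowledge Test, ISMI-10, Post-Traumatic Cognitions Inventory, SAM, FAST, PHQ-9, CIDI suicidal ideation | 9 |
| Nurse | CAPS-5, BPRS-4.0 | 2 |
| Device | Trauma challenge | 1 |

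- Participant-answered share: 9/12 = 75%.
- If the CIDI module counts as nurse-assessed, as it is at screening: 8/12 = 67%.
- If the device measure is dropped, since it is conditional on usability testing: 8/11 = 73% to 9/11 = 82%.
- If participant satisfaction is added to the 12: 9/13 = 69% to 10/13 = 77%.

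The majority is participant-answered in every version.

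**The case against.** The strongest reply is that only one word is wrong. Research staff can naturally be read as limited to those who conduct assessments, and the assessment schedule section confirms that reading. Nothing says that the researchers who randomize also assess. Unmasked self-report is inherent to any comparison of psychotherapy with usual care, so removing the word participants would change no data. The analyses are descriptive and exploratory, and participation, retention and fidelity do not depend on participant masking.

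Much of this stands. A reader might infer that masking is impossible throughout and that the whole trial is open-label, including CAPS-5 and BPRS-4.0. The documents do not support that, because masked nurses and data collectors and a separate qualitative interviewer are all planned.

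A reader might also infer that particular items will certainly unmask the assessors. That is not established either:

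- **Satisfaction.** Table 1 calls these intervention and healthcare ratings, which may cover both arms. No section says that a masked assessor collects them.
- **Chart.** No section says that assessors do the extraction. Visits up to 3 months can be fully extracted only at the end.
- **Strategy use.** Table 1 also marks it at enrolment, before allocation, so asking it there cannot reveal the arm. It discloses allocation only if assessors ask it of the intervention arm alone at follow-up. What is documented is the contradiction, not the leak.

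Three things do not fall to the reply: the participant-masking statement is untrue, the plan does not separate staff who know the arm from staff who assess, and Table 1 conflicts with the text on strategy use.

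**Conclusion.** The point holds for participants. The plan claims a masking that its comparison cannot deliver, and about 8 to 9 of the 12 two-arm outcomes are effectively unmasked as a result. The count assumes that the knowledge test, ISMI-10, cognitions inventory, FAST and PHQ-9 are answered by participants, since their mode is not stated outright.

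For assessors, masking is planned and achievable but weakly protected. CAPS-5 and BPRS-4.0 are best described as assessor-masked, with the caution that they rest on interviews with people who know their treatment and may mention it.

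The documents give no basis for estimating the size of any resulting bias. Given the descriptive feasibility aim, this is a worthwhile and nearly free correction and does not invalidate the study. Its main effect is on how the BREATHE-versus-TAU comparison may be read when the larger trial is planned.

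**What to change.** 1. Delete participants from the masking sentence in the Randomization section. Describe the trial as assessor-masked, and say that self-reported outcomes will be interpreted as unmasked.
2. State that anyone who runs the randomization, or who sees the arm in the study log or chart, does not assess outcomes. This covers chart extraction too.
3. Reconcile Table 1 with the Use of stress management strategies section: who is asked, by whom and when.
4. Have any arm-revealing items that remain at assessment visits (strategy use, intervention satisfaction) taken after the masked battery by the separate researcher already planned for the qualitative interviews.
5. Optionally, record each assessor's guess of allocation. This adds one item per visit and would give the future trial direct evidence on whether masking held.

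The cost is a few sentences of protocol text, a corrected table row and some reordering of tasks. The text places the separate researcher at the 1-month visit, so covering satisfaction at the post-assessment may need some extra staff time. The Trial status section says recruitment has not begun, so the changes can be made before any data are collected.

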### Quantitative data analyses

With a small sample size, the analyses will be descriptive and exploratory and will primarily be used to inform a future fully powered trial. We will calculate descriptive statistics to assess participation, retention, satisfaction, and fidelity. We will explore the relationship between covariates and baseline outcome scores and retention, satisfaction, and fidelity to identify any characteristics that might be associated with higher or lower implementation success. In addition, we will calculate summary statistics on all treatment mechanisms, mental health outcomes, and covariates of interest. We will investigate how scores on the outcome measures listed above change over time, paying particular attention to change between baseline and post-intervention scores and comparison between the intervention and the TAU groups. We will conduct bivariate analyses to assess the association between covariates and outcomes. Participant and caregiver reports will be analyzed separately. For continuous outcomes, we will use mixed-models with the participant as the random intercept to assess repeated measures change over time. This approach was selected because it models all available data regardless of whether individuals were missed at some time points. If deemed necessary, we will employ variable transformation techniques to improve the normality assumption. The analysis will include all participants who completed the baseline assessment and at least one treatment session, effects of outlier data inclusion in analyses will be assessed, and if necessary missing data will be handled using multiple imputation. Given the aim of the study to assess feasibility and implementation and the low sample size, differences in comorbidities will not be a main focus of analysis. Future larger iterations of the protocol will take these into account.

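### The outcome analysis is limited to participants who completed a treatment session, so the exploratory BREATHE versus TAU comparison is not between the groups as randomised

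*Protocol article*

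**What the plan says.** In the protocol article, the section *Quantitative data analyses* gives one rule for who is analysed: "The analysis will include all participants who completed the baseline assessment and at least one treatment session". The article names no all-randomised or intention-to-treat analysis. The same section applies the analysis to the arms, "paying particular attention to change between baseline and post-intervention scores and comparison between the intervention and the TAU groups", and explains the choice of a mixed model: "This approach was selected because it models all available data regardless of whether individuals were missed at some time points". It also sets the status of the results: "With a small sample size, the analyses will be descriptive and exploratory and will primarily be used to inform a future fully powered trial".

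On what a session is, the article says different things in different places:

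- *Intervention* describes BREATHE Ethiopia as five brief sessions.
- *Randomization* describes the comparator as "treatment as usual (TAU) which includes medication management and follow-up at the health facilities".
- *Feasibility trial assessment schedule* refers to TAU sessions, Table 1 there marks TAU in the column for sessions 1–5, and the text adds that "participants will be told they will complete five sessions and four interviews during the study", without limiting this to one arm.
- *Participation and retention* counts completed sessions for the intervention arm only, but counts completed assessments for everyone in the feasibility trial.

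**The concern.** Completing a session can only happen after allocation, and whether it happens may depend on the arm. Selecting on it means that the people compared are no longer those whom randomisation made comparable.

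The event also differs between arms. In BREATHE, a first session means taking up a new talking treatment about trauma. In TAU, it means coming to the routine contact that a patient would have had anyway. The people who fail these two tests need not be alike.

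The symptom and functioning comparison is meant to help plan a fully powered trial. If it describes starters only, the effect and variance estimates carried forward belong to a selected group. The future trial will randomise everyone eligible, including people who then do not start. The article also lets people who do not wish to go on with therapy remain in the assessments, so some outcome data from non-starters may be collected and then left out.

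**Working it through.** **Which reading of the rule applies?**

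1. If a treatment session means a BREATHE session, the rule can screen only the intervention arm. Taken literally, no TAU participant could qualify, which cannot be intended.
2. If it also covers TAU contacts, as the wording about TAU sessions and Table 1 suggests, the rule can be applied in both arms. One word then covers two different events, and the article defines no count of TAU sessions to apply it to.

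Either way, membership of the analysis set depends on something that happens after allocation and is not equivalent between arms.

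**Inputs from the article.** The target is n = 40, allocation is 1:1, and *Randomization* gives "45 participants to be randomized to account for potential dropout". No dropout rate is stated. The rate implied is 1 − 40/45 = 11.1%. A rate of 10% also leads to 45, since 40/0.90 = 44.4, rounded up. So 45 is consistent with a loss of roughly 10–11%, but this cannot be confirmed. With 45 randomised, the arms are about 22 and 23.

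**Inputs assumed.** The article gives neither of these:

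- f, the share of an arm that completes no session: 5–20%.
- g, the amount in SD by which starters do better than non-starters: 0.25–1.0.

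**Formula.** In one arm, the mean of all randomised equals (1 − f) × starter mean + f × non-starter mean. The starter mean therefore exceeds the mean of all randomised by f × g. With the same g in both arms, the arm difference shifts by

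(f_int − f_tau) × g.

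**If only BREATHE loses people** (f_tau = 0):

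| f_int | g (SD) | Shift (SD) | Shift / SE |
|---|---|---|---|
| 5% | 0.25 | 0.0125 | 0.04 |
| 10% | 0.5 | 0.05 | 0.17 |
| 20% | 1.0 | 0.20 | 0.67 |

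The SE is that of a simple difference in means in SD units: √(1/22 + 1/23) = 0.298, about 0.30. The number removed runs from 0.05 × 22 = 1.1 to 0.20 × 23 = 4.6, so about 1 to 5 people.

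**If both arms lose people:**

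- f_int = 20%, f_tau = 5%: 0.15 × 0.5 = 0.075 SD, to 0.15 × 1.0 = 0.15 SD.
- f_int = 5%, f_tau = 20%: −0.075 to −0.15 SD. The sign has reversed.

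If g differs between arms, the shift is f_int × g_int − f_tau × g_tau, so equal shares of non-starters would not guarantee a zero shift either.

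**The case against.** The strongest case on the other side is about scale. The analyses are declared exploratory, no powered test or effect threshold rests on this set, and the *Discussion* says that resources went deliberately to mixed-methods work rather than to a powered comparison. The middle case above is about one sixth of a standard error. This stands, and it lowers the severity. It does not turn a selected set into a randomised comparison.

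The objection also disposes of four stronger readings that a reader might infer:

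- *The rule inflates the BREATHE effect.* That needs TAU to lose nobody, or fewer people, and non-starters to do worse. The article gives neither, and the sign can reverse.
- *TAU has no sessions, so only BREATHE is screened.* The assessment schedule and Table 1 do attach sessions to TAU, and providers are told when a participant starts treatment or TAU. What remains is that a TAU session is undefined and not equivalent to a BREATHE session.
- *Non-starters vanish from the feasibility results.* Session counts start from everyone randomised to the intervention, and assessment retention covers all trial participants. *Qualitative interviews* also plans to sample people who dropped out of treatment. The loss falls on the outcome comparison, although the rule does not say which analyses it governs.
- *The rule contradicts the reason given for the mixed model.* That sentence concerns assessments missed at some time points. It does not promise to include everyone randomised. The two pull in different directions, but there is no outright contradiction.

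Finally, some non-starters may have no follow-up data under any rule, because a participant who misses a session and cannot be reached after repeated attempts may be discontinued from the study. This limits how much data the fix can recover.

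**Conclusion.** The point holds as a defect of the stated rule: the exploratory arm comparison is conditioned on a post-randomisation event that means different things in the two arms, and nothing else in the article restores an all-randomised comparison. The size and direction of the resulting bias are unknown. The range of about 0.01–0.20 SD rests on assumed values of f and g, on losses in BREATHE only, and on non-starters' outcomes being otherwise observed. It is smaller than one standard error throughout. No confirmatory error rate is affected. This should be fixed, because the estimates are meant for planning and the correction is cheap, but it is not critical to the feasibility aims.

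**What to change.** Replace the sentence with: *All randomised participants are analysed in the arm to which they were allocated, using every outcome assessment obtained, whatever the number of sessions attended.*

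Add one scheduling rule. The post-treatment assessment is timed from the last session, and TAU participants follow the dates of an intervention participant matched on enrolment date and health centre. A person who attends no session therefore has no assessment date, and neither does a TAU participant matched to that person. State how their dates are set, for example by extending the enrolment-date match already used for TAU.

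Keep the set of people with one session or more only as a labelled supplementary description, not for the arm comparison.

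The cost is one replaced sentence and one added scheduling rule, with no extra participants. The article reports that recruitment had not begun. Estimates may become slightly less favourable to BREATHE if its non-starters do worse, and the comparison will include people who received none of the intervention, as the full trial's comparison would.
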